### Quality control and secondary studies

#### Mass drug administration and focal mass drug administration intervention coverage

The population coverage of the MDA and fMDA interventions will be measured in two ways at each intervention round. Operational program coverage is defined as the proportion of individuals aged three-months-old and older, and households visited, offered the MDA and fMDA interventions within the target areas. Effective program coverage is defined as the proportion of individuals (aged three-months and older) that agreed to participate in the MDA and fMDA interventions among all individuals eligible to participate in the intervention in the target population.

The operational coverage will be estimated as the percent of the population that received a visit from the mass treatment teams to offer the MDA or fMDA interventions, among those eligible for inclusion. This will be obtained from a combination of MDA and fMDA program data and census enumeration data. Additionally, the proportion of individuals accepting the MDA and fMDA interventions aged three-months-old and older, among those eligible for inclusion in the intervention, will provide an estimate of the effective coverage of each program, as outlined below. Data for the denominator of individuals and households targeted for the intervention will be ascertained from the household enumeration for the sampling frame. Individual, household, and community level factors associated with coverage will be assessed using mixed effects logistic regression.

#### Participant adherence to dihydroartemisinin and piperaquine

A total of 150 individuals enrolled in the cohort study at round one, with a positive RDT in the MDA (n = 75) and fMDA (n = 75) rounds, plus another 150 individuals enrolled in the cohort study at round one, with a negative RDT in the MDA round, will be used to assess the level of adherence with the prescribed DHAp antimalarial regimen. Further details of the primary outcomes, sample size calculations, data collection methods, and the statistical analysis plan for this sub-study are provided in the Additional file 1.

#### Plasmodium falciparum parasite clearance following dihydroartemisinin and piperaquine

A total of 150 individuals enrolled in the cohort study at round one, with a positive RDT in the MDA (n = 75) and fMDA (n = 75) rounds, will be used to assess parasite clearance following DHAp. Further details of the primary outcomes, sample size calculations, data collection methods, and the statistical analysis plan for this sub-study are provided in the Additional file 1.

#### Acceptability of dihydroartemisinin and piperaquine in the community

The assessment of community acceptability of the MDA and fMDA interventions will be ascertained using a mixed methods approach. Acceptability of the interventions will be assessed quantitatively during the baseline and follow-up parasite surveys among WRA. Focus groups will also be used to qualitatively assess community perceptions of the acceptability of the MDA and fMDA interventions, including community members who consented and participated, as well as those who refused. Further details of the acceptability study are provided in the Additional file 1.

### Study timeline

Figure 5 shows the timeline for the major activities for the primary study of evaluating the impact of the MDA and fMDA interventions on reducing malaria morbidity. The study started with the randomization of HFCA in early 2014. The baseline parasite survey was conducted between April and May of 2014 during the peak malaria transmission season. The first MDA and fMDA rounds were conducted between November and December 2014, with round two scheduled for February 2015. The longitudinal cohort started at the same time as the first MDA and fMDA round in November 2014; the cohort will continue monthly follow-up through November 2015. Routine data on confirmed OPD malaria cases started in January 2014 and will continue through 2015. The follow-up parasite survey is scheduled to take place between April and May 2015, during the peak malaria transmission season.

**Fig. 5 Fig5:**
[figure not shown]
Study timeline for major activities. *MDA*: mass drug administration; *fMDA*: Focal mass drug administration; *LLIN*: Long-lasting insecticide-treated nets; *IRS*: Indoor residual spraying; *HFCA*: Health facility catchment area; *HMIS*: Health management information system

### Ethical approval

Ethical approval in Zambia for the primary and secondary studies has been obtained from the Research Ethics Committee (REC) at the University of Zambia (study reference 007-03-14) and the Zambian Medicines Regulatory Authority (trial number CT 033/12). Ethical approval was also obtained from the Tulane Institutional Review Board (IRB; study number 59208573) and Western IRB (covering PATH-MACEPA; study number 1146551).

## Discussion

In line with the goals of the Zambia National Malaria Strategic Plan, robust comparisons of the effectiveness and cost-effectiveness of available mass treatment approaches, including MDA and fMDA interventions using DHAp, are needed. Toward that end, this study will assess the relative effectiveness of two mass treatment approaches at reducing the malaria burden beyond already implemented interventions of LLINs and IRS. The relative effectiveness of MDA and fMDA with DHAp will be established against a comparison of no mass treatment (standard of care) in areas with higher and lower malaria parasite prevalence using a community randomized control trial. The findings of this study will provide the Zambia NMCC and their partners with guidance on the most effective and cost-effective strategies to further reduce the size of the malaria parasite reservoir, malaria transmission, and the incidence of clinical disease in southern Zambia, and will hopefully show evidence of local transmission interruption.

The strengths of this trial include the fact that a rigorous study design (a CRCT) will be used to assess the impact of the MDA and fMDA interventions, as compared to a control of no mass treatment (standard of care). The study is also powered to assess differences between each treatment group (MDA and fMDA) and the control group, within areas of high and low transmission, with 80 % statistical power. The study uses robust measures of malaria parasite infection at the point of contact using RDTs, as well as PCR, for detecting low-density parasite infections, as part of the parasite surveys and the longitudinal cohort. The study also uses multiple methods for measuring malaria-related outcomes, including malaria parasite infection prevalence ascertained from a pre- and post-parasite survey, malaria parasite infection incidence using a longitudinal cohort of individuals selected randomly from within each HFCA, and confirmed malaria case incidence throughout the study using routine health management information system (HMIS) data in the study area. Buffer areas between contiguous HFCAs with different interventions are being used to limit contamination and misclassification bias. Measures of the quality of the implementation of the MDA and fMDA interventions will be obtained to help with the interpretation of results; these include MDA and fMDA population coverage, adherence to DHAp, parasite clearance after DHAp, community perceptions and acceptability of the MDA and fMDA interventions, and multiple measures of operational coverage. Lastly, a rigorous analysis plan will be followed, for assessing the impact of each intervention compared to a control group, while accounting for potential contextual and confounding factors within random-effect regression models.

Noted weaknesses of this trial include a less than ideal number of community randomization units (N = 60), especially when stratified by high (n = 30) and low (n = 30) transmission strata. The sample size within the high and low transmission strata will only allow the detection of approximately a 50 % reduction in parasite prevalence and infection incidence between intervention groups, with 80 % statistical power; the threat of a type two error is therefore higher than ideal. The primary analysis will be based on the intention-to-treat principle; there is potential for misclassification of exposure using this approach. Secondary analysis using a per-protocol approach will be used mitigate any misclassification of exposure. And lastly, there is always the potential for error in the measurement of outcomes, exposure to the interventions, and potential confounding factors in such a large and complex trial. We have gone to considerable length to try and minimize such error through the use of electronic data capture systems in the field and robust diagnostic methods.

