### Randomization sequence generation and allocation concealment

Pre-existing maps of HFCAs were used to classify households as belonging to a specific HFCA, which serve as the unit of randomization. To ensure balance across large and small HFCAs, which could potentially affect the quality of program implementation and other related unobserved confounding factors, HFCAs were characterized as having either a large or small population catchment size. This classification was based on a cut-point obtained from the mean population catchment size across the 60 HFCAs. Within the high and low transmission strata and the large and small population catchment size classifications, the random allocation rule will be used to assign HFCAs to the fMDA-DHAp, MDA-DHAp, or control group. As a result of this process and the stratification outlined above, the 60 total HFCAs are split into 10 HFCAs per treatment group (MDA, fMDA, and control) in the high transmission strata (n = 30 HFCAs), and 10 HFCAs per treatment group (MDA, fMDA, and control) in the low transmission strata (n = 30 HFCAs).

After allocation, the appropriate intervention will be implemented in the entire catchment area according to treatment group assignment. Allocation of study arms will not be blinded to the deliverers of the intervention or to the main investigators, as delivery of the intervention precludes the possibility of allocation concealment. However, data collectors in the follow-up parasite prevalence survey, as outlined below, will be blinded to allocation. All primary analyses will also be blinded to analysts by the use of concealed code for the study arm variables in the final dataset.

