#### Baseline and follow-up household parasite surveys

A cross-sectional survey of households in the high transmission season (April to May) in 2014, and again in 2015, will be conducted to obtain an unbiased sample of children under six-years-old (excluding those under one-month-old) for measuring primary outcome one (parasite prevalence). All children under six-years-old that slept in the house the night before the survey will be included in the sample. A complete enumeration and geo-referencing of all households in the study area serves as the sampling frame. To mitigate contamination between exposure groups (MDA, fMDA, and control) in the household sampling frame, sampling buffers of at least 1.5 km were derived for all HFCAs using GIS, in order to maintain an adequate distance between households in HFCAs with different exposure assignments (resulting in a gap of at least 3 km between sampled households in different HFCAs). A simple random sample of 47 households was then drawn within each of the 60 HFCAs (equal allocation sampling), to obtain the total sample size of 2,820 households in the 2014 baseline survey, after restricting the sampling frame for sampling buffers in GIS. The same sampling procedure will be used for the follow-up parasite survey in 2015.

Selected households during each survey round will be visited by trained survey data collectors that will administer a standardized survey questionnaire using mobile phones, based on the standard Malaria Indicator Survey (MIS) questionnaire [15]. Capillary blood from a finger prick from all children in selected households will be collected for detection of a malaria parasite infection by RDT, microscopy, and PCR. Children found to have a positive RDT will be treated for their infections with AL as per the Zambia National Malaria Treatment Guidelines [14].

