#### Longitudinal cohort

*P. falciparum* infection incidence will be measured by following a cohort of individuals aged three-months-old and older (and not pregnant) for measuring primary outcome indicator two, the *P. falciparum* infection incidence rate (Fig. 4). Individuals within each HFCA and treatment group, within the high and low transmission strata, will be preselected from those registered in the household roster in selected households during the baseline household parasite survey between April and May 2014. Enrollment of individuals will start during round one (November 2014) of the fMDA and MDA interventions, and concurrently among individuals during round one in control areas visited for assessing RDT positivity.

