### Rapid diagnostic test positivity during campaign rounds

As described above under the MDA and fMDA intervention descriptions, all individuals aged three-months-old and older in these HFCAs will be tested by RDT for detecting malaria parasite infections; this will then be used for ascertaining primary outcome four (RDT positivity) in each HFCA. RDT positivity in control areas during each of the two rounds of the MDA and fMDA interventions in 2014, and again in 2015, will be obtained through comparing RDT positivity among individuals tested as part of the monthly control cohort during the months when the MDA and fMDA rounds occur.

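### Outcome four (RDT positivity) compares whole catchments in the MDA and fMDA arms with a control cohort drawn only from inside the 1.5 km buffer, so its contrast may be biased by an unknown amount

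*Protocol article*

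**What the plan says.** All references are to the Protocol article.

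- **Discussion (strengths):** "Buffer areas between contiguous HFCAs with different interventions are being used to limit contamination and misclassification bias". The sentence is not limited to particular outcomes.
- **Baseline and follow-up household parasite surveys:** the buffer is defined for the household sampling frame: "sampling buffers of at least 1.5 km were derived for all HFCAs using GIS", leaving at least 3 km between sampled households of different HFCAs. The 47 households per HFCA were drawn "after restricting the sampling frame for sampling buffers in GIS".
- **Longitudinal cohort:** in every arm, cohort members are "preselected from those registered in the household roster in selected households during the baseline household parasite survey between April and May 2014".
- **Randomization sequence generation and allocation concealment:** delivery is not buffered: "the appropriate intervention will be implemented in the entire catchment area according to treatment group assignment".
- **Rapid diagnostic test positivity during campaign rounds (data collection):** in MDA and fMDA areas, "all individuals aged three-months-old and older in these HFCAs will be tested by RDT for detecting malaria parasite infections", and these tests supply outcome four. The control value comes from the monthly control cohort in the months of the rounds.
- **Rapid diagnostic test positivity during campaign rounds (sample size):** about 5,000 people per HFCA in each intervention group, against 375 control cohort members per stratum.
- **Statistical analysis plan:** outcome four is compared at each round by a chi-square test and by logistic models with a random HFCA intercept, and trends across rounds are then examined. No common geographic zone is imposed.

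**The concern.** RDT positivity is one of the four listed primary outcomes. Randomisation balances whole HFCAs. It does not balance the inner zone of control HFCAs against the inner zone plus border strip of treated HFCAs. A random intercept and unspecified confounder adjustment do not make the two populations the same, and the chi-square test does not attempt to.

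By the article's own reasoning, border households are the ones most exposed to a neighbouring HFCA's assignment. They enter the treated arms of outcome four and are left out of its control arm.

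- **Round two:** spillover from less intensively treated neighbours would raise positivity in treated border households, and the control value would contain no matching border component.
- **Round one:** testing accompanies the first treatment, so the arms should not yet differ. Any baseline difference between core and border would appear as a difference between arms, and the trend across rounds would start from it.

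**Working it through.** **1. Which households feed outcome four**

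| Arm | Source | Area |
|---|---|---|
| MDA, fMDA | everyone aged three months or older tested in the campaign | whole HFCA |
| Control | cohort, drawn from baseline survey households | inside the 1.5 km buffer |

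The planned numbers fit the whole-catchment reading. The Study site section gives just over 330,000 people, and 330,000 / 60 = 5,500 per HFCA. Testing about 5,000 of them is 5,000 / 5,500 = 91 %, which leaves little room for an unstated core restriction.

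**2. Reproducing the plan's figures**

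Hayes–Moulton formula for unmatched clusters, with c clusters per arm, one-sided 5 % (z = 1.645), and m0, m1 people per cluster:

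V = p0(1−p0)/m0 + p1(1−p1)/m1 + k²(p0² + p1²)

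power = Φ( |p0−p1| / √(V/(c−1)) − 1.645 )

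- *Survey, m = 39:* 30 to 18 % with k = 0.31 needs c = 9.99; 10 to 4 % with k = 0.41 needs c = 10.00. Both reproduce the planned 10.
- *Outcome four, high stratum* (30 to 20 %, k = 0.31, m0 = 375/10 = 37.5, m1 = 5,000, c = 10): V = 0.005600 + 0.000032 + 0.012493 = 0.018125; 0.10/√(0.018125/9) = 2.228; power 72.0 %.
- *Outcome four, low stratum* (10 to 5 %, k = 0.41): V = 0.002400 + 0.0000095 + 0.002101 = 0.004511; power 72.2 %.

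The stated 80 % for outcome four is not reproduced. That gap is a separate matter with nothing to do with the buffer; 72 % serves here only as the reference for costing the fix.

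**3. What the mismatch could do (illustration on assumed values)**

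Let f be the border share of tested people, L the share of the effect lost there, and r the ratio of border to core prevalence. The article gives none of the three.

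- *Round two, high stratum:* observed positivity = 20 % + 10 % × f × L. With f = 0.1 and L = 0.25 it is 20.25 %; with f = 0.4 and L = 0.5 it is 22 %. The shift is 0.25 to 2 percentage points toward the null.
- *Round one, no treatment effect, core at 30 %:* whole-catchment positivity = 30 % × (1 − f + f × r). With f = 0.4 it is 26.4 % at r = 0.7 and 33.6 % at r = 1.3; with f = 0.2 it is 28.2 % and 31.8 %. The sign depends on r.

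**4. Cost of restricting the treated arms to the inner zone**

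| Campaign records per HFCA | Power, high | Power, low |
|---|---|---|
| 5,000 | 72.0 % | 72.2 % |
| 2,500 | 72.0 % | 72.1 % |
| 1,000 | 71.8 % | 71.9 % |
| 500 | 71.4 % | 71.5 % |

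The treated-arm sampling term is tiny (0.000032 of 0.018125 at 5,000 records). Between-cluster variation and the 37.5 controls per HFCA dominate.

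**5. Cohort against cohort**

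With m0 = m1 = 37.5, V is 0.005600 + 0.004267 + 0.012493 = 0.022360 (high) and 0.002400 + 0.001267 + 0.002101 = 0.005768 (low). Power is 64 % and 63 %. This comparison is like for like but weaker, so it suits a sensitivity analysis.

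**The case against.** **Dilution is not shown.** A reader might infer that the mismatch dilutes the treatment effect. The article does not support that as a statement of fact: round one has no effect to dilute, and a core–border difference in prevalence can push either way. This objection stands.

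**No power loss can be read off.** A reader might model a circular catchment, treat its whole 1.5 km rim as contaminated and arrive at a serious loss. Such a figure comes from its inputs. Edges on Lake Kariba, on the study boundary or beside an HFCA in the same arm do not face another assignment. Border residents of treated HFCAs are offered the intervention themselves, and an MDA border may face fMDA, which is also active. For example, with catchment radii of 5 to 10 km, half the rim facing another arm and a quarter of the effect lost there (all assumed), power would be 67 to 69 % against 72 %. This stands too.

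**The Discussion sentence is not false.** It is true of the survey and, through sampling, of the cohort, and the Abstract names contamination as a limitation. That is fair: the sentence is too broad, and the general caveat does not tell the reader that outcome four is treated differently by arm.

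**Outcome three is unbuffered as well.** It is, but its facility counts are handled alike in all arms, so it has no between-arm mismatch and is not part of this point.

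**Whole-catchment results follow the randomised unit.** They do on the treated side only, because the control side is already restricted. A geographic restriction applied alike to all arms remains intention to treat.

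**A filter leaves other differences.** A campaign census would still be set against a repeatedly tested, non-pregnant cohort whose RDT-positive members are treated. This stands, and is why a cohort-versus-cohort comparison should accompany the filter.

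**Conclusion.** The mismatch follows directly from the text: outcome four compares whole catchments in the treated arms with the buffered core in the control arm. The contrast may be biased by an unknown amount. At round two the likely direction is toward the null, provided that neighbouring HFCAs in other arms cause spillover. At round one it can go either way, provided that core and border prevalence differ. The illustrated shifts (0.25 to 2 points at round two; 26.4 to 33.6 % against 30 % at round one) rest wholly on assumed border shares, losses and prevalence ratios and are not estimates for this trial. No loss of power is claimed. The survey and cohort outcomes are unaffected. The correction is worth making because it removes a between-arm population difference from a primary outcome at almost no cost.

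**What to change.** - **Rapid diagnostic test positivity during campaign rounds, and Statistical analysis plan:** make the main outcome-four comparison from MDA and fMDA campaign records of households inside the same 1.5 km inner zone that supplied the control cohort. Show the whole-HFCA figure as secondary.
- **Statistical analysis plan:** add, as a sensitivity analysis, RDT positivity in the cohort across all three arms in the months of the rounds. The cohort is sampled alike in every arm and is tested by RDT at enrolment and every four weeks.
- **Discussion:** say that the buffer applies to the survey, the cohort and the restricted outcome four.

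The cost is a geographic filter on campaign records, using the household geo-referencing and buffers that already exist, plus one analysis of data already planned. Fewer campaign records are used, but power changes by 0.6 points (high) and 0.7 points (low) even at 500 per HFCA.

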## Trial status

The study is ongoing. The baseline parasite survey was completed in April to May 2014. The first round of the MDA and fMDA intervention was completed in November to December 2014; the longitudinal cohort started at the same time. The second round of the MDA and fMDA intervention is scheduled for February 2015 (concluding in mid-March 2015). The follow-up parasite survey is scheduled for April to May 2015, while monthly longitudinal follow-up is scheduled to continue through November 2015.

## Abbreviations

AL: Artemether lumefantrine
CRCT: Cluster randomized control trial
DHA: Dihydroartemisinin
DHAp: Dihydroartemisinin plus piperaquine
DOT: Directly observed therapy
fMDA: Focal mass drug administration
HFCA: Health facility catchment area
ICER: Incremental cost effectiveness ratio
IPD: Inpatient
IRB: Institutional review board
IRS: Indoor-residual spraying
LLIN: Long-lasting insecticide-treated mosquito net
MDA: Mass drug administration
NMCC: National Malaria Control Center
OPD: Outpatient
RDT: Rapid diagnostic test
REC: Research ethics committee
PCR: Polymerase chain reaction
WHO: World Health Organization
WRA: Women of reproductive age
